# Establishment of optimal exercise therapy using near-infrared spectroscopy monitoring of tissue muscle oxygenation after therapeutic angiogenesis for patients with critical limb ischemia: A multicenter, randomized, controlled trial

**DOI:** 10.1016/j.conctc.2020.100542

**Published:** 2020-02-04

**Keywords:** Critical limb ischemia, Arteriosclerosis obliterans, Therapeutic angiogenesis, Optimal exercise therapy, Tissue muscle oxygen saturation, Near-infrared spectroscopy, CLI, critical limb ischemia, PAD, peripheral artery disease, ASO, arteriosclerosis obliterans, BM-MNC, bone marrow-derived mononuclear cells, TAO, thromboangiitis obliterans, NO, nitric oxide, eNOS, endothelial nitric oxide synthase, VAS, visual analogue scale, CT, computed tomography, TcPO_2_, transcutaneous oxygen pressure, SPP, skin perfusion pressure, WIQ, walking impairment questionnaire, RHI, reactive hyperemia index, StO_2_, thenar tissue oxygen saturation, NIRS, near-infrared spectroscopy, TOI, tissue oxygenation index, nTHI, normalized tissue hemoglobin index, ΔO_2_Hb, change in oxygenated hemoglobin concentration, ΔHHb, change in deoxygenated hemoglobin concentration

## Abstract

Critical limb ischemia (CLI) is a potentially life-threatening condition that involves severely reduced blood flow to the peripheral arteries due to arteriosclerosis obliterans (ASO) of the limbs or a similar condition. CLI patients must undergo revascularization to avoid amputation of the lower limbs and improve their survival prognosis. However, the outcomes of conventional surgical revascularization or endovascular therapy are inadequate; therefore, establishing further effective treatment methods is an urgent task. We perform therapeutic angiogenesis using autologous bone marrow-derived mononuclear cells in clinical practice and demonstrated its safety and efficacy for CLI patients for whom conventional treatments failed or are not indicated. Exercise therapies must be devised for CLI patients who have undergone therapeutic angiogenesis to save their limbs and improve survival. Because evidence regarding the efficacy and safety of exercise therapy for CLI patients is lacking, we plan to perform a prospective trial of the efficacy and safety of optimal exercise therapy following therapeutic angiogenesis for CLI patients.

The trial will enroll 30 patients between 20 and 79 years with Rutherford category 4 or 5 CLI caused by ASO who will undergo therapeutic angiogenesis. Participants will be randomly allocated to receive either optimal exercise therapy or fixed exercise therapy. Those receiving optimal exercise therapy will undergo tissue muscle oxygen saturation monitoring using near-infrared spectroscopy while performing exercises and will be prescribed optimal exercise therapy. The optimal amount of exercise will be determined on day 8, 31, 61, 91 and 181 after therapeutic angiogenesis.

**Ethics and dissemination:**

This protocol was approved by the Institutional Review Boards of Kyoto Prefectural University of Medicine. In accordance with the Helsinki Declaration, written informed consent has been obtained from all participants prior to enrollment. The results of this trial will be disseminated by publication in a peer-reviewed journal.

**Trial registration:**

This trial is registered at http://www.umin.ac.jp/ctr/index.htm (identifier: UMIN000035288).

## Introduction

1

Critical limb ischemia (CLI) is the end stage of peripheral artery disease (PAD), which occurs when peripheral artery stenosis or occlusion severely reduces blood flow, thereby causing the appearance of resting pain, gangrene and ulceration of the limbs. Patients with lifestyle-related diseases, older individuals, and those undergoing hemodialysis are at high risk. However, the underlying cause varies widely, with diseases including arteriosclerosis obliterans (ASO), thromboangiitis obliterans (TAO), and vasculitis due to collagen diseases eventually leading to CLI. The yearly major limb amputation rate for CLI is approximately 30%; in approximately 20% of cases, the condition reportedly persists despite successful revascularization or other standard treatment [1]. The survival prognosis is extremely poor, with 1-year survival rates of 70%–80% and 5-year survival rates of 50% [1]. Cardiovascular events are one of the important prognostic factor in CLI patients. Thus, CLI leads to a high rate of limb amputation and is potentially fatal. Moreover, as its prevalence increases with age, the number of patients with CLI associated with ASO is also expected to increase rapidly. Therefore, the establishment of further methods of treatment other than the current standard therapies is an urgent task. Therapeutic angiogenesis using autologous bone marrow-derived mononuclear cells (BM-MNC) had been undertaken in clinical practice and demonstrated its safety and efficacy for no-option CLI patients caused by ASO, TAO, and vasculitis due to collagen diseases for whom conventional treatments failed or are not indicated [[2], [3], [4], [5], [6], [7]]. However, the long-term survival rate and limb salvage rate were lower in CLI patients associated with ASO after therapeutic angiogenesis compared to those associated with TAO or collagen diseases [7]. Therefor it is necessary to further improve the survival rate and limb salvage rate in CLI and ASO patients.

Although exercise therapy for ASO patients with claudication is recommended in several guidelines, the therapy for CLI and ASO patients is not recommended from the view point of worsening of limb ischemia and deterioration of their wound [1,8]. However, exercise therapy can be introduced after therapeutic angiogenesis, and may provide the effect of preventing physical function deterioration and progression of lower limb ischemia and arteriosclerosis. Therefore, we should establish appropriate exercise intensity and frequency that do not lead deterioration of lower extremity ischemia and wound for CLI patients after therapeutic angiogenesis. Herein, we have planned a clinical trial to identify the direct efficacy of appropriate exercise therapy for limb ischemia for patients who have undergone therapeutic angiogenesis.

### Endpoints

1.1

The primary endpoint is the change in the maximum walking distance 6 months after therapeutic angiogenesis (day 181) compared with baseline. The secondary endpoints are changes in the following parameters day 181 compared with baseline: pain-free walking distance; resting pain measured using the Visual Analogue Scale (VAS), on which 0 cm indicated pain-free or no pain and 10 cm indicated the most severe pain; skeletal muscle mass of the ischemic limb measured by a body composition analysis and lower limb contrast-enhanced computed tomography (CT); transcutaneous oxygen pressure (TcPO_2_) and skin perfusion pressure (SPP) of a dorsal or plantar region in an affected lower limb; walking impairment questionnaire (WIQ) scale; Fontaine class and Rutherford category; reactive hyperemia index (RHI) score (vascular endothelial function); muscle strength (grip strength and isometric knee extension strength); vascular volume below the knee of the ischemic limb measured by lower limb contrast-enhanced CT; number of ischemic ulcers on the ischemic limb; and maximum area (length × width) of ischemic ulceration on the ischemic limb.

Safety endpoints were the incidence, severity, and seriousness of adverse events; overall survival duration; incidence of major limb amputation; and time to major amputation.

## Materials and methods

2

### Study design

2.1

This is a multicenter, open-label, randomized, controlled trial.

### Study setting

2.2

Five hospitals have agreed to participate in this trial. This protocol (protocol number: CQARD-CAR-180701) has been approved by the Institutional Review Boards of Kyoto Prefectural University of Medicine. In accordance with the Helsinki Declaration, written informed consent has been obtained from all participants prior to enrollment.

### Participants

2.3

The inclusion criteria are as follows: patients registered for therapeutic angiogenesis using autologous bone marrow-derived mononuclear cells (BM-MNC) implantation conducted as a clinical trial under the Act on the Safety of Regenerative Medicine; CLI patients with Rutherford category 4 or 5; patients capable of undergoing near-infrared spectroscopy (NIRS) measurements at the specified sites; and patients of either sex between 20 and 79 years who have provided written consent to participate in the trial based on the will of the patients themselves and/or the understanding and approval of their families after having received a full explanation of the advantages and disadvantages arising from exercise therapy and the advantages and disadvantages arising from not undergoing exercise therapy by means of an informed consent form.

The exclusion criteria are as follows: patients who do not provide informed consent or who are unsuitable for the trial because of emotional considerations, even if the disease and procedure are suitable; remaining life expectancy of less than 1 year because of another comorbid condition; untreated limb with Fontaine class III or worse; undergoing treatment for active malignancy; ischemic heart disease that has not been treated with revascularization; untreated severe diabetic retinopathy; serious infection; serious hepatic impairment or serious renal impairment (excluding chronic maintenance dialysis patients); serious hematological disorder such as leukopenia or thrombocytopenia or severe anemia necessitating blood transfusion; pregnancy, potential pregnancy, or breastfeeding; other severe acute or chronic medical or psychiatric conditions or abnormal clinical test results for which participation in the trial may result in increased risk or that may affect the interpretation of the trial results; unable to engage fully in exercise therapy due to cerebrovascular diseases, limb amputation, or other diseases; and deemed unsuitable to participate in the trial by an investigator or sub-investigator for any other reason.

### Randomization

2.4

Patient enrollment and randomization will be performed at the central data center of Kyoto Prefectural University of Medicine. The eligible participants will be randomly allocated in a 1:1 ratio using a truncated stratified permuted block randomization with stratification for institution to receive either optimal exercise therapy or fixed exercise therapy (Fig. 1).

**Fig. 1 fig1:**
[figure not shown]
Study flow chart.

### Treatment regimens and hemodynamic evaluation of the ischemic limb

2.5

#### Evaluation

2.5.1

1.Maximum walking distance and Pain-free walking distance

Patients walk quickly on a flat surface, and the maximum walking distance (m) of which they are capable despite leg symptoms (such as claudication and pain) will be measured. Pain-free walking distance (the maximum distance they can walk without leg symptoms) will also be measured at the same time.2.Treadmill walking test monitoring tissue muscle oxygenation by NIRS

In this trial, we use NIRS (NIRO-200NX; Hamamatsu Photonics Co., Ltd.) to evaluate tissue muscle oxygenation in the target limb. During the treadmill walking test, we continuously evaluate by NIRS oxygenated hemoglobin concentration (ΔO_2_Hb), change in deoxygenated hemoglobin concentration (ΔHHb), a tissue oxygenation index (TOI) and normalized tissue hemoglobin index (nTHI) which are indicators of tissue muscle oxygenation. The NIRS fiber-optic probe and light detector will be attached to the anterior tibialis and lateral gastrocnemius muscles of the treated leg. Measurements will be started 1 min before the treadmill walking test with standing position, and ΔO_2_Hb, ΔHHb, and variations in nTHI and TOI will be measured over time at a sampling frequency of 1 Hz. After the end of the treadmill walking test, the recording will be continued until dissociation between ΔO_2_Hb, ΔHHb and nTHI converges.

Following the partly modified method of Gardner et al. [9], exercise intensity will start at a speed of 0.5 km/h and increase after 1 min in 0.5-km/h increments up to a maximum of 5.0 km/h; then, the patient will continue to walk at this rate (5.0 km/h) (maximum 10 min). The treadmill walking test will be ended if symptom limitations** are reached. Then, the patient will remain seated at rest until the ΔO_2_Hb, ΔHHb, and nTHI recover and symptoms improve, and the time from the end of the treadmill walking test until recovery from symptoms (symptom recovery time) will be measured.

**Reasons for ending the test are defined as severe leg symptoms (such as claudication or pain), chest pain, unbearable dyspnea, leg spasm, unsteadiness, excessive sweating, facial pallor or cyanosis, or TOI <30% with a low nTHI.

#### Exercise protocol

2.5.2

We divided into 2 groups: optimal exercise therapy group and fixed exercise therapy group.

#### Fundamental exercise

2.5.3

We will start fundamental exercise without load on the ischemic wound (consisted of warming up, leg stretches and resistance training) from day 2 after therapeutic angiogenesis and continue until the end of the protocol in both groups.

#### Exercise protocol in the optimal exercise therapy group

2.5.4

From day 8, optimal exercise therapy which consists of Treadmill walking will be started in addition to the fundamental exercise (Fig. 2). Based on the treadmill walking test and hemodynamic evaluation by NIRS, exercise at a walking speed of 80% of the walking speed at the end of the treadmill test will be prescribed as the exercise regimen. During the protocol therapy period, patients of the optimal exercise therapy group are instructed to walk at this exercise intensity according to this regimen for at least 30 min and at least three times a week (home-based exercise). Exercise regimen will be re-evaluated by treadmill test with using NIRS on day 8, 31, 61, 91 and 181 after therapeutic angiogenesis. (Fig. 2).

**Fig. 2 fig2:**
[figure not shown]
Manual of exercise therapy for each group. NIRS, near-infrared spectroscopy.

#### Exercise protocol in the fixed exercise therapy group

2.5.5

In addition to the fundamental exercise (Fig. 2), the patients in the fixed exercise therapy group will be allowed free walking for disuse syndrome preventing from day 8 and will be given exercise instructions to continue walking on the comfortable speed before discharge. Subsequently, they will visit attend outpatient appointments a hospital at the same timing points as those used for the optimal exercise therapy group (day 31, 61, 91, and 181 after therapeutic angiogenesis); again, they will receive the same type of instruction.

Optimal exercise therapy will be implemented as follows. First, the maximum walking distance will be measured, and the level of challenge on the treadmill walking test will be adjusted accordingly. During the treadmill walking test, patients will undergo tissue muscle oxygenation monitoring with NIRS.

#### Exercise management during the protocol therapy period

2.5.6

In both group, the amount of exercise or daily activities performed during the protocol therapy period will be monitored with an Actiwatch (Philips, N.V., USA), which generates a signal corresponding to the level of movement and its frequency by the accelerometer and records the movement as an activity count. Participants of the optimal exercise therapy group will receive instructions regarding exercise approximately once per week. During the protocol therapy period, record books will be issued, and either the patients themselves or a family member will record their daily amounts of exercise and activity levels. The attending physician will check these during study period to hospital visits by the participants and evaluate the compliance of exercise therapy.

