### Statistical considerations

2.8

The safety analysis set will comprise all those enrolled patients who underwent the protocol therapy. The efficacy analysis set will comprise patients in the safety analysis population other than those found to be ineligible after enrollment. For the primary endpoint, the change (difference) in the maximum walking distance 6 months after therapeutic angiogenesis compared with baseline between the two groups will be compared using a one-sided *t*-test. For the secondary endpoints, the following parameters will be analyzed using a *t*-test: change (difference) in pain-free walking distance (the distance walked by the patient before leg pain starts), Visual Analogue Scale (VAS) score, skeletal muscle mass of the ischemic limb measured by body composition analysis and lower limb contrast-enhanced CT, TcPO_2_, SPP, WIQ scale, RHI score (vascular endothelial function), and muscle strength (grip strength, isometric knee extension strength), vascular volume below the knee of the ischemic limb measured by lower limb contrast-enhanced CT, the number of ischemic ulcers on the ischemic limb, and the maximum area (length × width [cm^2^]) of ischemic ulceration on the ischemic limb. For changes in the Fontaine class and Rutherford category, the differences between the two groups before and after therapy will be compared using the Wilcoxon rank sum test.

For safety endpoints, the occurrence, frequency, and severity of all adverse events occurring during the trial will be summarized for the safety analysis set. The time from therapeutic angiogenesis to either major amputation or death from any cause will be used to estimate amputation-free survival rates for the two groups by the Kaplan-Meier method. A similar analysis will be conducted for overall mortality using the time from therapeutic angiogenesis to death from any cause.

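### About weekly instruction in the optimal arm, against four post-discharge visits in the fixed arm, creates a risk that non-serious adverse events are recorded unequally

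*Protocol article*

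**What the plan says.** Section 2.1 describes the design: "This is a multicenter, open-label, randomized, controlled trial".

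The two arms have different planned contact:

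- **Optimal arm (2.5.6):** "Participants of the optimal exercise therapy group will receive instructions regarding exercise approximately once per week". The article does not say how this instruction is delivered or whether adverse events are asked about then. This arm also has treadmill re-evaluations on days 8, 31, 61, 91 and 181 (2.5.4).
- **Fixed arm (2.5.5):** patients "will be given exercise instructions to continue walking on the comfortable speed before discharge", and then attend as outpatients on "day 31, 61, 91, and 181 after therapeutic angiogenesis". The section says that these are the same time points as in the optimal arm. No weekly contact is stated for the fixed arm.

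Section 1.1 lists the safety endpoints: "Safety endpoints were the incidence, severity, and seriousness of adverse events; overall survival duration; incidence of major limb amputation; and time to major amputation". Section 2.8 plans that "the occurrence, frequency, and severity of all adverse events occurring during the trial will be summarized for the safety analysis set". It names no between-arm test for adverse events. Amputation-free survival and overall mortality are to be estimated by Kaplan-Meier.

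Section 2.5.6 also provides activity monitoring in both arms and daily record books. The books are described as holding exercise and activity; no adverse-event item is mentioned.

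**The concern.** Someone who is contacted every week about walking has more chances to mention a sore leg, a change in a wound or a stumble than someone seen at intervals of 30 to 90 days. Staff and patients know the allocation. If such remarks become adverse-event records, the recorded count depends on how often patients are contacted as well as on how often events occur.

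The events most open to this are the ones the trial needs to learn about. The Introduction and Discussions explain that exercise is not currently recommended in critical limb ischemia because it may aggravate limb ischemia, and the Introduction adds deterioration of the wound. The Conclusions name safety as an aim. The likely direction of any distortion is to make the optimal arm look less safe. A false excess could be read as harm, or a real excess could be explained away as closer contact. If the source of each event is not recorded at the time, the two explanations are hard to separate afterwards.

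**Working it through.** The article gives no figure for safety ascertainment, so there is no stated value to reproduce. The check is arithmetic on the stated schedule, followed by an illustration that rests on assumptions.

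**Contact counts**

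- Inputs: optimal exercise starts on day 8 (2.5.4); instruction is about weekly (2.5.6); outpatient visits are on days 31, 61, 91 and 181 (2.5.5). Assumption: the weekly instruction runs over the whole of day 8 to day 181.
- Span: 181 − 8 = 173 days; 173 / 7 = 24.7 weeks, so about 25 weekly contacts.
- Fixed arm after discharge: 4 visits. Ratio: 24.7 / 4 = 6.2 to 1. The optimal arm has the same four visit days as well.
- Fixed-arm intervals from day 8: 31 − 8 = 23, 61 − 31 = 30, 91 − 61 = 30 and 181 − 91 = 90 days. Part of the first interval is before discharge; the discharge day is not given.

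**Does 2.8 neutralise the difference?** The summary covers all adverse events occurring during the trial. Nothing shown limits it to the shared visits, so an event volunteered at a weekly contact would count as the section is worded.

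**What unequal capture would do (assumed values)**

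If the true risk p is the same in both arms and the shares captured are c1 (optimal) and c0 (fixed), the apparent risk ratio is (p × c1) / (p × c0) = c1 / c0, whatever p is. Take p = 40%, c1 = 90% and the target of 15 patients per arm from 2.6. The expected number of optimal-arm patients with a recorded event is 15 × 0.40 × 0.90 = 5.4. For the fixed arm:

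- c0 = 90%: 5.4 patients, ratio 1.0
- c0 = 80%: 15 × 0.40 × 0.80 = 4.8 patients, ratio 0.90 / 0.80 = 1.125
- c0 = 60%: 15 × 0.40 × 0.60 = 3.6 patients, ratio 0.90 / 0.60 = 1.5
- c0 = 50%: 15 × 0.40 × 0.50 = 3.0 patients, ratio 0.90 / 0.50 = 1.8

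None of the values of p, c1 or c0 comes from the article. The range shows how the mechanism works and is not an estimate for this trial.

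**The case against.** The strongest reply is that the decisive link is not in the text. The weekly contact is for exercise instruction. The article does not say that adverse events are asked about or recorded then, and the full protocol, which is not shown, may already tie collection to the common visits with the same questions in both arms. This stands, and it is why the point is worded as a risk. A reader might infer that adverse events are in fact ascertained unequally and that the safety comparison is biased; the article does not support that.

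Three further objections also limit the point:

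- **No planned test or pooling.** Section 2.8 neither pools the arms nor tests between them for adverse events. Even so, a safety summary in a two-arm randomized trial will be read by arm.
- **Hard outcomes.** Death and major amputation hardly depend on how often a patient is contacted, and the same holds for serious events. A claim about the safety endpoints as a whole would be too broad.
- **Size.** A reader might try to quantify the gap by supposing that an event is recorded only if a contact falls while it lasts. For a 7-day event, weekly contacts on days 8 to 176 catch 169 of 174 onset days (97%), and the four visits catch 28 of 174 (16%). Adding the shared visits to the optimal arm raises its figure to 100%. This ignores recall at visits and lasting signs such as wounds, so it is an extreme case and should not be quoted as the size of the effect.

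It could also be objected that moving weekly-contact events to a separate listing would thin out the experimental arm's main safety table, in a trial concerned with harm from exercise. That is a fair objection to such a remedy. The fix below leaves every event in the main summary.

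**Conclusion.** The point holds as a risk created by the design as written. One arm has about 25 additional planned contacts, the trial is open-label, and the adverse-event summary is not restricted to the visits that both arms share. It applies to non-serious, transient events. It rests on two assumptions: that the weekly instruction continues through the treatment period, and that at least some events mentioned there reach the adverse-event record.

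The size cannot be computed from the article. Under assumed capture of 90% against 80% to 50%, equal true risks would appear as ratios of 1.125 to 1.8; with equal capture the ratio is 1.0. The primary endpoint, the sample size, and the survival and amputation analyses are not touched.

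**What to change.** In 2.8:

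1. Keep the all-source adverse-event summary for the safety analysis set as planned.
2. State that non-serious events are elicited with the same checklist (leg pain, wound change, falls) in both arms at the common visits on days 31, 61, 91 and 181.
3. Record for each event whether it came from a common visit or a weekly contact.
4. Add a by-arm table restricted to events elicited at the common visits, and name it as the basis for comparing non-serious events between arms.

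Serious events, major amputation and death continue to be counted from every source. If the full protocol already sets such a collection rule, stating it in 2.8 and adding the table is enough.

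The cost is one source field, one checklist and one extra table. No event leaves the main safety summary, and treatment, contact schedule and sample size do not change. The source field has to be in use from the start, because the source is hard to reconstruct later.
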